## Abstract

**Background:**

A SARS-CoV-2 infection can lead from asymptomatic through to critical disease in a dynamic and unpredictable course within a few days. The challenge in outpatient monitoring the highly contagious COVID-19 disease during the ongoing pandemic is to filter severe courses followed by admission to hospital with the aim of preventing an overburdening of clinics. However, little is known of the effect of risk factors on the course of the infection of outpatient patients. To support general practices in managing high risk patients, we designed a COVID-19 surveillance and care tool (CovidCare). It includes an initial assessment of yet known risk factors and symptoms and a continuous telephone monitoring of signs and symptoms. This study aims to investigate the effects of different risk factors on the course of the COVID-19 disease, utilisation of different health care services and to gain insights into the utilisation of CovidCare in general practices.

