### Eligibility criteria {10} and informed consent

All GPs who participate in general-practice centred care (GP-centred care) by the AOK Baden-Württemberg care are eligible for using the CovidCare-module within the CareCockpit software. The eligible practices are informed by the GP-centred care contract partners about the possibility to use CovidCare for the care of confirmed and suspected COVID-19 patients.

Prerequisites are the online registration and participation in an online training including exam questions for the handling of the software. After the successful completion of the exam, general practices can download the software.

All general practices who have successfully completed the exam and who download the software are automatically provided with an invitation for participation in the CovidCare study as well as an information leaflet and a participation form.

General practices can participate in the CovidCare study by sending the signed participation form to the study central office (Department of General Practice and Health Services Research, University Hospital Heidelberg).

Additional time expenditure for GP-practices for participation in the study concern information of eligible patients, obtaining the informed consent as well as the weekly data transfer. Time expenditure for this study depends on the number of patients a general practice can include in the study.

The study population comprises of COVID-19 patients treated in general practices who meet the inclusion criteria. The study population for the process evaluation consists of GPs, VERAHs (Care Assistant in General Practice (*Ver*sorgungs*a*ssistentin in der *H*ausarztpraxis)) and patients participating in the CovidCare study.

The following groups of patients are eligible for participating in the study:

COVID-19 patients aged 18 or older (as per definition patients with symptoms of an infection of any severity and positive test for SARS-CoV-2), who are in domestic isolation* and who have at least one risk factor**

OR

2.Patients aged 50 and older with a clinically urgent suspicion of COVID-19 (such as acute respiratory symptoms of any severity), without verification of SARS-CoV-2 and who have at least one risk factor**/***

*Domestic isolation: includes persons for whom the authorities highly recommend further social distancing beyond the restrictions as currently ordered.

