### Outcomes

The primary outcome is hospitalisation due to COVID-19. The following indicators have been identified as secondary outcomes:

Diagnosis of pneumonia in confirmed and suspected COVID-19 patients [14].Utilisation of palliative care by confirmed and suspected COVID-19 patients during quarantine or stay at hospital.Mortality rate of confirmed and suspected COVID-19 patients (death at home, death in hospital, death in long-term care institution).Anxiety in confirmed and suspected COVID-19 patients using the Generalized Anxiety Disorder Index (GAD-2) [15].Identification of predictive risk factors for the outcomes such as hospitalisation, intensive care and mortality.

For the process evaluation we chose an exploratory sequential design. The process evaluation consists of a qualitative strand and a quantitative strand.

Overall, for the process evaluation we use the RE-AIM framework according to Glasgow and colleagues [16] to assess reach, efficacy, adoption, implementation and maintenance of the CovidCare surveillance and care tool. Table 1 provides an overview of the outcomes, indicators and methods/instruments of the process evaluation according to the RE-AIM framework.

**Table 1 Tab1:** Concept of the process evaluation

Outcomes	Indicators (examples)	Methods/Instruments
1) Reach The extent to which patients are reached by the implementation of CovidCare as well as the number of patients who are willing or refused to participate in CovidCare.	• How have patients been approached • Number of patients approached • Number of patients willing to participate in CovidCare • Patients: Reasons for refusal and drop-out, exclusion rate • Number of contacts per patient (i.e. telephone monitoring, particularly in the critical phase as defined by the RKI as a proxy whether GPs treat their patients according to guidelines) • Characteristics of participating patients	S, I, DB
2) Efficacy The efficacy of the CovidCare-module includes positive and negative impacts/effects for patients and HCP as well as the patients’ quality of life and the patients and the HCP’s satisfaction with the intervention.	• Positive and negative effects on patients’ quality of life, perception of (quality of) care, disease coping • Effects on health care personnel in managing Covid-19 patients • Satisfaction of HCP and patients with CovidCare • Comparison with patients with Covid-19/suspected cases but WITHOUT additional risk factors or aged >50	S, I, DB

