For participation in the questionnaire survey, eligible GPs and VERAHs will be provided with a study information, informed consent forms and paper-based questionnaires. Interested persons will send the filled-in questionnaire and signed consent form in an enclosed post-paid envelope to the study central office.

As for patients, all participating patients will be informed about participation in an interview and in the questionnaire survey by the VERAH after the final consultation. The VERAH will send an expression of interest form and a post-paid envelope to the patients interested in participating in an interview and/or the questionnaire survey. The patient sends the expression of interest forms to the study central office using the enclosed post-paid envelope and will then be contacted by the study team via telephone to get more information about the study, answer open questions and schedule an interview. The study team will send the informed consent forms for the interview and the questionnaire respectively (each in duplicate), the study information and one post-paid envelope to the patient who will sign and return all informed consent forms to the study central office for study participation. A member of the study team will then sign all informed consent forms and return one copy (of the informed consent) to the patient and send him/her the questionnaire via post.

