### Data collection and management

#### Plans for assessment and collection of outcomes

Data sources for the evaluation are data collected within the CovidCare-module within the CareCockpit software in general practices in Baden-Wurttemberg. The CareCockpit software, developed and licensed by the Department of General Practice and Health Services Research at the University Hospital Heidelberg, is designed for case management in general practices and is currently used in approx. 700 general practices in Baden-Wurttemberg. The CovidCare-module therefore is an extension of the electronic patient record in general practices and supports GPs to take care of confirmed and suspected COVID-19 patients in a structured and standardized way. The CovidCare-module has been recently developed and is implemented in general practices within GP-centred by the AOK Baden-Württemberg.

The following data will be recorded from general practices: ID, practice identification number, date and time of the dataset created.

In an initial assessment and telephone monitoring, potential risk (risks) factors are recorded and symptom progression is documented.

Consequently, the following data will be recorded from patients:

ID, gender, date of the informed consent, treatment ended (yes/no), date of end of treatment as well as reasons, request to delete data (yes/no), date and time of the dataset created; data on their individual assessments (examples: ID, date of assessment, ID of VERAH who conducts the assessment, age, diabetes, cardiovascular data, data on pulmonary diseases, liver diseases, immune system, medication, cancer diseases, other diseases, hospitalisation, obesity, smoking, pneumococci, influenza, medication regimen) and monitoring, when available (examples: ID, date and time and place of the dataset created, ID of VERAH who conducts the monitoring, anxiety, medication, patients’ condition as well as symptoms and course of the disease, cured, deceased).

Data sources for the process evaluation are questionnaires and qualitative telephone interviews with GPs, VERAHs and patients using self-developed semi-structured interview guides (see Additional files 1 and 2) and paper-based questionnaires according to the RE-AIM framework (see Table 1) as well as data from the CovidCare-module. Self-developed questionnaires will be presented to the ethics committee in an amendment.

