#### Data management, Confidentiality

The evaluating institution (Department of General Practice and Health Services Research, University Hospital of Heidelberg) receives pseudonymized data only and cannot assign data to individuals.

Data collected in the CovidCare-module are secured in the general practices.

Pseudonymized data from patients who have given their informed consent is transferred to the study central office weekly. Data include all pseudonymized data collected in the initial assessment and the telephone monitoring as described in the intervention description.

Patients in each general practice are given a sequential number, which is linked to the corresponding general practice in the data. For the purpose of the identification of general practices, they export their unique license key as well as their practice identification number. In the study central office, a list linking the license key and the BSNR to a practice name and address data is stored separately and secured.

Data will be transferred via a secure unidirectional way (Zentraler Daten-Austausch-Container/ Kryptographie- und Transfer-Modul, ZeDaC-KTM). The ZeDaC-KTM interface allows for flexible, universal, and secure data exchange between health care organisations and their partners (here: Dept. of General Practice and Health Services Research). Hybrid encryption is used, which combines the benefits of asymmetric (public-key cryptosystem RSA (4096 bit)) and symmetric encryption (Advanced Encryption Standard (AES) 256 bit). The key length lies above the recommendations of the Federal Office for Information Security. This means that data that is temporarily stored on the ZeDaC-KTM server for the purpose of data transfer is encrypted and not readable. Only when data is collected from the server by the study central office, the encryption is reversed.

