Digital data from questionnaires, interviews, and the CovidCare software module is stored on database-servers at the Department of General Practice and Health Services Research, University Hospital Heidelberg and are only accessible by the study team. Servers are in a separate room that can only be accessed by authorized personnel of the IT-team. Servers are not connected to the internet and cannot be accessed externally. All system users must have personalized access to the network of the University Hospital Heidelberg. Additionally, users must have a personalized user account in order to access the server. Data on the server is secured on the data storage of the data center of the University Hospital Heidelberg on a daily basis.

Data is secured for 10 years after the completion of the study or until a participant withdraws his/her consent to participate and demands to have data already collected destroyed, and will then be destroyed irretrievably.

Anonymized data only will be used for publications.

The existing data protection concept of the CareCockpit, proven by all partners will be used.

The principle investigator is responsible for data processing.

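### Staff questionnaires travel with the signed consent to the department that developed the tool, so answers are identifiable on receipt; this does not fit the unqualified pseudonymity statement and risks softened ratings

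*Protocol article*

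**What the plan says.** The staff survey is on paper. Under Recruitment {15} and Implementation, the return procedure is: "Interested persons will send the filled-in questionnaire and signed consent form in an enclosed post-paid envelope to the study central office". No second envelope, separate recipient or code on the questionnaire is mentioned.

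The recipient is identified under Eligibility criteria {10} and informed consent, where practices join "by sending the signed participation form to the study central office (Department of General Practice and Health Services Research, University Hospital Heidelberg". Under Plans for assessment and collection of outcomes, the same department is the software's source: "The CareCockpit software, developed and licensed by the Department of General Practice and Health Services Research at the University Hospital Heidelberg". The abstract adds that the authors themselves designed the CovidCare tool that runs within it.

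Under Data management, Confidentiality, this department is named as the evaluating institution, and the article says that it "receives pseudonymized data only and cannot assign data to individuals". Later in that section: "Digital data from questionnaires, interviews, and the CovidCare software module is stored on database-servers".

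Table 1 (Outcomes) lists among its efficacy indicators "Satisfaction of HCP and patients with CovidCare", and among its implementation indicators the problems met and the adaptations needed in daily use. The survey is one source for both. The survey data are to be analysed descriptively (Statistical methods).

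**The concern.** Two things follow if the return procedure is carried out as written.

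First, a statement about confidentiality is not true of one data stream. Whoever opens the envelope at the central office holds a person's signature and that person's answers together.

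Second, the answers are an appraisal of a product, sent under the respondent's own name to the group that made it. The central office also describes itself as being in constant contact with the sites (Adverse event reporting and harms), so this is a continuing working relationship. Softened criticism is a recognised risk in such a setting. The study has no comparator and the survey is only described, so no step in the stated analysis would reveal or offset a shift if one occurred.

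**Working it through.** No sample size, alpha, expected satisfaction rate or misreporting rate for the survey is given, so there is no figure of the plan to reproduce. The check is a comparison of sections.

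1. **What arrives together?** The staff procedure names the completed questionnaire and the signed consent and refers to an enclosed envelope in the singular. Read plainly, both come in one mailing.
2. **Who receives it?** The study central office, which the eligibility section equates with the Heidelberg department.
3. **What else does that department do?** It developed and licenses CareCockpit (Plans for assessment and collection of outcomes). It is the evaluating institution (Data management, Confidentiality). Developer, recipient and evaluator are therefore the same body.
4. **Does this fit the pseudonymity sentence?** That sentence speaks of what the institution *receives* and says that nothing else reaches it. Staff answers received with a signature are not pseudonymised at that moment. Separating and coding the forms afterwards would protect the stored data, but it would not make the sentence true of what was received.
5. **Could the sentence concern module data only?** The sentences that follow it describe data kept in the practices, weekly transfer, patient numbering and the encrypted interface, all of which concern the module. But the sentence carries no such limit, and the same section later covers questionnaire and interview data.
6. **How do the other routes compare?** Patients return their consent first and are posted the questionnaire afterwards, so the one-envelope point does not apply to them. The list that links practices to names and addresses is stored separately. Separation of identity and data is thus already practised elsewhere in the study.
7. **Which results depend on the staff survey?** The satisfaction and problem indicators in Table 1, both drawn from survey, interviews and database together. Hospitalisation, the secondary outcomes and the risk-factor models come from the module.

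**Size.** If a share *d* of staff is dissatisfied and a fraction *f* of them answers favourably because they can be identified, reported satisfaction is too high by *d* × *f*. Neither input is in the documents. With assumed ranges of *d* = 0.10 to 0.40 and *f* = 0 to 0.30, the result runs from 0.10 × 0 = 0 to 0.40 × 0.30 = 0.12, that is, from 0 to 12 percentage points. The range includes zero and rests wholly on assumption, so it cannot be used as an estimate.

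**The case against.** The best defence is that the pseudonymity sentence was only ever about module data. Its surroundings support this. Elsewhere the central office telephones staff who volunteer for an interview, and the interviewer countersigns their consent, so a sentence meant to cover the process evaluation would fail there as well. This largely stands, and it is why the sentence should be narrowed rather than treated as a broken promise. A reader might infer that staff were assured their ratings would be pseudonymous; the article contains no such assurance addressed to them.

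It can also be said that what happens after the envelope is opened is operational detail that an article leaves to the full protocol. That is fair for handling after receipt, and no gap is alleged there. The point concerns a procedure that the article does state.

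A third argument is that a code key held in the same department leaves the developer able to link answers to people. This is correct: coding lowers exposure without ending it.

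Finally, the indicators in Table 1 are triangulated, and interviewees are known to the team whatever envelope is used. This limits the reach of the point. It does not remove it, because a better protected survey would be the less exposed of the two channels through which staff give their views.

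**Conclusion.** A small point stands. Staff answers are identifiable on receipt by the department that developed and evaluates the tool; this does not fit the unqualified pseudonymity wording, and it creates a risk of more favourable ratings of satisfaction and fewer reported problems in the staff survey. It rests on reading the return procedure as a single mailing, which is its plain sense.

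Two stronger readings are not supported. One is that the ratings *are* biased in the tool's favour: the documents give a reason to expect such a tendency, but no evidence of its presence or size. The other is that adverse-event information is compromised by the envelope: the section on adverse events assigns its exploration to the interviews, not to the questionnaire.

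The primary outcome, the risk-factor models, the interviews and the patient survey are unaffected. This is an inexpensive improvement to a descriptive component, not a threat to the study's main results.

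**What to change.** - **Recruitment {15} and Implementation:** have staff return the signed consent and a questionnaire bearing a code and no name in separate sealed envelopes. Store the code key apart, out of reach of those who enter and analyse the survey, and tell respondents so in the study information. Respondents must know of the protection for it to affect how they answer.
- **Data management, Confidentiality:** limit the pseudonymity sentence to CovidCare-module data.

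The article says that the self-developed questionnaires will go to the ethics committee in an amendment, so both changes can be included in that submission.

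The cost is a code list to maintain and one extra envelope for each respondent to seal. Re-linkage stays possible, which is needed if a participant withdraws and asks for data to be destroyed. For that reason the change reduces the risk and does not remove it.

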### Who will be blinded {17a} Procedure for unblinding if needed

Not applicable, as this is not a blinded trial.

### Data collection and management

#### Plans for assessment and collection of outcomes

Data sources for the evaluation are data collected within the CovidCare-module within the CareCockpit software in general practices in Baden-Wurttemberg. The CareCockpit software, developed and licensed by the Department of General Practice and Health Services Research at the University Hospital Heidelberg, is designed for case management in general practices and is currently used in approx. 700 general practices in Baden-Wurttemberg. The CovidCare-module therefore is an extension of the electronic patient record in general practices and supports GPs to take care of confirmed and suspected COVID-19 patients in a structured and standardized way. The CovidCare-module has been recently developed and is implemented in general practices within GP-centred by the AOK Baden-Württemberg.

The following data will be recorded from general practices: ID, practice identification number, date and time of the dataset created.

In an initial assessment and telephone monitoring, potential risk (risks) factors are recorded and symptom progression is documented.

Consequently, the following data will be recorded from patients:

ID, gender, date of the informed consent, treatment ended (yes/no), date of end of treatment as well as reasons, request to delete data (yes/no), date and time of the dataset created; data on their individual assessments (examples: ID, date of assessment, ID of VERAH who conducts the assessment, age, diabetes, cardiovascular data, data on pulmonary diseases, liver diseases, immune system, medication, cancer diseases, other diseases, hospitalisation, obesity, smoking, pneumococci, influenza, medication regimen) and monitoring, when available (examples: ID, date and time and place of the dataset created, ID of VERAH who conducts the monitoring, anxiety, medication, patients’ condition as well as symptoms and course of the disease, cured, deceased).

Data sources for the process evaluation are questionnaires and qualitative telephone interviews with GPs, VERAHs and patients using self-developed semi-structured interview guides (see Additional files 1 and 2) and paper-based questionnaires according to the RE-AIM framework (see Table 1) as well as data from the CovidCare-module. Self-developed questionnaires will be presented to the ethics committee in an amendment.

Interviews will be audio-recorded and then transcribed by research assistants of the Department of General Practice and Health Services Research, University Hospital Heidelberg. Interviews will be complemented by sociodemographic characteristics of the participants and information on the associated general practices. Questionnaires are digitalized for the purpose of data analysis.

